### The UYB training program

Health visitors are trained in the UYB on a two-day course, followed by two supervisions lasting three hours each, and two brush-ups lasting 1.5–3 h. The two-day course includes lectures on infant socioemotional development according to the topics described in the UYB manual as well as an introduction to the dialogue cards. Furthermore, the health visitors practice the sharing of age-specific and research-based knowledge to parents by watching video clips of ADBB screenings with infants scoring both below and above cutoff on the ADBB. More specifically, for each of the five areas from the ADBB, the health visitors practice describing the following three themes in regard to the video clips: 1. Infant behavior and underlying needs, 2. How parents can support infant socioemotional development (including what they are already doing, and what they should continue with), 3. Why this area is important for infant longitudinal development (e.g. how breaks from eye contact are needed for the child to self-regulate and engage in eye contact again). Finally, health visitors are introduced to the video library. After the two-day course, the health visitors should start using the UYB during their routine home visits.

Approximately two and four weeks after the course, the health visitors attend two three-hour group supervision sessions. During these supervisions, the implementation of the UYB in the health visitor’s daily practice is discussed and the health visitors watch more video clips of ADBB screenings. The purpose of the supervisions is for the health visitors to continue practicing their use of the mandatory dialogue card and articulating the infant’s behaviors as expressions of needs according to each of the five areas described on the card and in the manual.

At the two-day course and the two supervisions, the health visitors’ attendance is registered. Completion of the UYB training requires min. 80% attendance to the training and supervisions.

Around five months after the second group supervision, the health visitors attend the first brush-up session, which has the same format and content as the three-hour group supervisions. Finally, the health visitors attend a second (online) 1.5–2 h brush-up. This brush-up takes place approximately 5–9 months after the first brush-up and focuses on the health visitors discussing their daily practice and use of the UYB.

### Measures including outcomes

Different types of data are collected throughout the project: Data from questionnaires completed by parents and health visitors and data from the health visitors’ register.

The questionnaire data from parents and health visitors are collected and managed using REDCap electronic data capture tools hosted at University of Copenhagen [42, 43]. The parents are send questionnaire packages when their children are 2, 4, 7, and 11 months old, and it is possible to complete the questionnaires in both Danish and English. In a lottery, three gift cards are drawn each month, and the parents have the chance of winning a gift card worth approximately 76$ from a store selling baby items each time they answer one of the questionnaire packages. All participants are send a small present for the child, a children’s book worth approximately 6$, if they complete all four questionnaires. The health visitors are send questionnaires 1, 3, 6, and 12 months after they have finished the second UYB supervision. The health visitors are not offered any rewards for answering the questionnaires.

The data from the health visitors’ register is obtained after the children have turned 12 months. Data from this register is only obtained if at least one of the parents has given consent.

### Background information and control variables

*Background information* about the parents is obtained as part of the 2- and 11-months questionnaire. At 2 months, this information includes questions about parental age, gender, ethnicity, educational background, employment status, income, relationship status, smoking, persons living in the household, the birth weight of the child, birth complications, and siblings to the child. At 11 months, parents are asked about breastfeeding, parental leave, and parental involvement with the child.

*Parental depressive symptoms* will be measured using the Edinburgh Postnatal Depression Scale (EPDS; [44]) or the Gotland Male Depression Scale (GMDS; [45]). The EPDS is a screening instrument for postnatal depression, which has primarily been validated in female samples. The EPDS contains 10 items assessing the presence of depressive symptoms in the past seven days (e.g. “I have felt sad and miserable”). Each item is rated on a four-point scale from “No, not at all” (= 0) to “Yes, quite a lot” (= 3). GMDS is a screening tool for male depression and consists of 13 items assessing whether the respondent’s behavior has changed during the last month (e.g. “More aggressive, outward-reacting, difficulties keeping self-control”). Each item is rated on a 4-point Likert type scale from “Not at all” (= 0) to “Extremely so” (= 4) [46]. For both questionnaires, items are summed to a total score with higher scores reflecting higher levels of depressive symptoms. These questionnaires are routinely given to parents typically around 8 weeks postpartum as part of the health visitors’ mental health screening program. The parents fill in the questionnaires during the health visitor’s visit in either a web-based or paper-and-pencil manner. The EPDS and GMDS data will be obtained from the health visitors’ register.

*Intensity of UYB implementation* will be measured as a combination of data obtained from the health visitors’ register and questions asked to the parents about the different UYB elements. The data obtained from the register will be the number of ADBB-screenings during the first year of life, and whether the health visitor was certified in UYB at the time of the screening. The questions asked to the parents include number of home visits during the first year of life, and whether they have seen the dialogue card(s), followed UYB on social media, or used the video library. The questions regarding the number of home visits, the dialogue card(s), and the social media will be asked at 11 months while the questions regarding the video library will be asked at 2, 4, 7, and 11 months.

### Primary study outcome

*Parenting competence* will be measured using the Parenting Sense of Competence Scale (PSOC; [47, 48]). In the current study, the Danish version of the PSOC translated by Lange et al. [49] is used. The most commonly used tool for measuring parental competence is the PSOC [50]. The PSOC was originally developed by Gibaud-Wallston in 1977, and the scale has subsequently been revised and used in a number of studies (for instance, [51–53]). The PSOC consists of 17 items rated on a 6-point Likert type scale from “Strongly agree” to “Strongly disagree”. The scale has two subscales, with eight of the items being summed together to calculate the Skill/Knowledge subscale and the remaining nine items being summed together to create the Valuing/Comfort subscale. A total score is calculated by summing all 17 items (of which nine are reverse-scored), with higher scores indicating a higher level of parenting competence [54]. Parenting competence is measured at 2, 4, 7, and 11 months.

### Secondary study outcomes

*Parental reflective functioning* will be measured using the Parental reflective functioning questionnaire (PRFQ; [14]), a self-report measure of the parental ability to reflect upon the mental states of oneself and the child. In this study, we use the 15-item version of the PRFQ, which has been validated in a sample of Danish mothers of infants [55]. The items are rated on a 7-point Likert type scale going from “Completely disagree” (= 1) to “Completely agree” (= 7). Items are summed together to form three subscales measuring different aspects of parental mentalizing: (a) Interest and curiosity in the child’s mental states (e.g. “I like to think about the reasons behind the way my child behaves and feel”), (b) Certainty about the child’s mental states (e.g. “I can completely read my child’s mind”), and (c) Pre-mentalizing modes, i.e. difficulties recognizing the child’s mental states (e.g. “My child cries around strangers to embarrass me”). Parental reflective functioning is measured at 4, 7, and 11 months.

*Parental representational mind-mindedness* will be assessed using the written response to the following open-ended question: “We would like you to describe your child using your own words. You can write exactly what comes to mind, and you can write as little or as much as you like.” The response is used to code parental mind-mindedness, i.e. the ability to generate mental descriptions to the child in writing. Parental mind-mindedness is coded based on the guidelines described in [56]. To control for opacity, mind-mindedness is calculated as the number of mental descriptors divided by the total number of attributes used. Parental mind-mindedness is measured at 2, 4, 7, and 11 months.

*Parenting stress* will be measured using the Parenting Stress Index, Fourth Edition – short form (PSI-4-SF; [57]), a 36-item questionnaire measuring stress in relation to being a parent. Each item is rated on a 5-point Likert type scale from “Strongly disagree” (= 1) to “Strongly agree” (= 5). The PSI-SF provides a total score and three subscales: (a) Parental distress, measuring stress related to the parent’s experience of parenting and/or his or her parenting abilities (e.g. “I feel trapped by my responsibilities as a parent”), (b) Parent–child dysfunctional interaction, measuring stress related to the parent’s experience of interactions with his or her child (e.g. “I expected to have closer and warmer feelings for my child than I do, and this bothers me”), and (c) Difficult child, measuring stress related to the parent’s experience of his or her child’s characteristic (e.g. “My child makes more demands on me than most children”). Parenting stress is measured at 4 and 11 months.

*Infant socioemotional development* will be measured using the Ages & Stages Questionnaires®: Social-Emotional, Second Edition (ASQ:SE-2; [58]). The ASQ:SE-2 questionnaire for children aged 9 to 14 months contains 27 items assessing the presence of different socioemotional behaviors (e.g. “Does your baby smile at you and other family members?”). There are three choices for each item: “Most of the time” (= 0), “Sometimes” (= 5), and “Rarely or never” (= 10). In addition, the parent can check a “concern” option for each item, which adds 5 points to the score for that item. Items are summed to a total score with higher values reflecting less optimal socioemotional development. Empirically derived cutoffs are available to determine whether the child’s socioemotional development appears to be on schedule, in the monitor zone, or in need for further evaluation [58]. Infant socioemotional development is measured at 11 months.

*Infant social withdrawal* will be measured using the Alarm Distress Baby Scale (ADBB; [15]). The ADBB is an observer-rated screening tool consisting of eight items: Facial expressions, Eye contact, General level of activity, Self-stimulating gestures, Vocalizations, Briskness of response to stimulation, Relationship, and Attraction. Each item is rated on a 5-point scale from “Absolutely normal” (= 0) to “Very obvious abnormal behavior” (= 4). Items are summed to a total score with higher scores indicating more social withdrawal. A cutoff of ≥ 5 may be used to identify infants showing clinical levels of social withdrawal [15, 23–25]. The ADBB data will be obtained from the health visitors’ register and will be based on the ADBB observations performed by the health visitors at the home visits (see Table 2).

*Parental media use and infant screen time* will be measured using a short questionnaire developed by the authors focusing on the use of different types of screens (television, tablets, smartphones, etc.) in the families (Additional file 1). The questions address the parent’s screen time during the infant’s awake time (total minutes per day), the infant’s screen time (total minutes per day), and the parent’s perception of technoference in the parent–child relationship (number of disturbances per day). Media use is measured at 2, 4, 7, and 11 months.

*Information about infant development* is assessed at 11 months using a short questionnaire developed by the authors (Additional file 2). Parents are asked to what degree they have been informed about each of the following topics by their health visitor during their infant’s first year: (a) My child’s physical development, (b) My child’s nutrition and sleep, (c) My child’s emotional development, (d) How I manage my child’s emotions, (e) My child’s social competences and development, and (f) How I support my child’s social development. In this study, we are interested in whether parents have received more information about the last four topics.﻿ 

Table 3 shows an overview of all the questionnaires that are completed by the parents at the different measurement points.

**Table 3 Tab3:** Points of measurements of control variables, primary and secondary outcomes

Measures	T1 (2 months)	T2 (4 months)	T3 (7 months)	T4 (11 months)	Obtained from the health visitors’ register
*CAU and UYB*					
Background information, incl. Socioeconomic status (SES)	X			X	
Depressive symptoms (EPDS and GMDS)					X
Parenting Sense of Competence Scale (PSOC)	X	X	X	X	
Parental Reflective Functioning Questionnaire (PRFQ)		X	X	X	
Parental Mind Mindedness (MM)—written description	X	X	X	X	
Parenting Stress Index, Fourth Edition—short form (PSI-4-SF)		X		X	
Ages and Stages Questionnaire®: Socio-Emotion, Second Edition (ASQ:SE-2)				X	
Alarm Distress Baby scale (ADBB)					X
Parental media use and infant screen time	X	X	X	X	
Information about infant development				X	
*Only UYB*					
Intensity of UYB implementation				X	

*CAU* Care As Usual. *UYB* Understanding Your Baby

### Sample size

We used the R package simr [59] to conduct a power analysis. We wanted to be able to detect a small effect size (Cohen’s *d* = 0.2; [60]) using a linear mixed model with one predictor (i.e. group status) and three covariates (all continuous). Using a power of 0.80 and a significance level of 0.05, 690 participants are needed in order to detect a small effect. Assuming that 25% of the participants drop out after intake and before the endpoint, a total of 920 participants will have to be recruited. A participant is considered to have dropped out when they actively withdraws from the study or does not answer any of the questionnaires.

### Statistical methods

The analyses of both primary and secondary outcomes will be conducted under the intention to treat principle where the participants are analysed according to their control CAU/intervention UYB status. However, as a secondary analysis, we will also conduct analyses where the actual intervention participation is taken into account (i.e. whether the families in the UYB group have been given the intervention by the health visitors). Thus, we will perform a contamination adjusted intention to treat analysis [61] which compliments the intention-to-treat approach by producing a better estimate of the effect of the UYB intervention.

The primary endpoint is PSOC at 11 months postpartum. The level of significance will be 5%, two-tailed [62]. The primary comparison of UYB and CAU interventions is analysed using linear mixed models with the health visitor as the second order variable. This is done to account for the correlation induced by the same health visitor conducting the CAU and UYB intervention for multiple families. We will control for maternal educational level in years, maternal level of depressive symptoms, and maternal age in years.

Secondary outcomes will be analysed in the same way as the primary outcome. Binary and categorical outcomes will be analysed with mixed logistic and multinomial logistic regressions, respectively, and continuous outcomes with mixed linear regression analyses. For outcomes where we are interested in the individual variance across time points, generalized estimating equations will be employed. All the analyses will be adjusted for the abovementioned covariates. As multiple tests will be conducted, we will both assess significance using the 5% significance level and adjust for multiple testing using the Bonferroni-Holm method [63].

For the tertiary outcome, we investigate whether some subpopulations benefit more from the UYB intervention. These subpopulations will be defined as disadvantaged families (e.g. based on background information such as employment status, income, etc.) versus advantageous families as well as families with a more intensive UYB implementation. In practice, we will test for significant subpopulations-group status interaction effects using linear moderation analyses (as otherwise described above).

Regarding missing data, the first step will be to delete the group status variable to be blinded. If more than 95% of the observations are complete, a complete case analysis will be conducted. Otherwise, data-driven, pragmatic choices will be made in selecting a few background variables (e.g. educational level, parental age at birth, level of depressive symptoms) to see which ones are strong predictors of missing status and then use multiple imputation to handle missing data [64]. Imputations will be conducted using the software package ‘mice’ [65].

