**Methods:**

This study evaluates the efficacy of the intervention Understanding Your Baby (UYB) compared to Care As Usual (CAU) in 10 Danish municipalities. UYB aims at promoting parental competence in new parents by supporting them in noticing their infants’ behavioral cues and interpreting them in terms of mental states. Participants will be approximately 1,130 singletons and their parents. Inclusion criteria are first-time parents, minimum 18 years old, living in one of the 10 municipalities, and registered in the Danish Civil Registration Register (CPR). Around 230 health visitors deliver the UYB as part of their routine observation of infant social withdrawal in the Danish home visiting program. During an interaction between the health visitor and the infant, the health visitor articulates specific infant behaviors and helps the caregivers interpret these behaviors to mental states. The study is a controlled parallel group study with data obtained at four time points in two phases: First in the control group receiving the publicly available postnatal care (CAU), secondly in the intervention group after UYB implementation into the existing postnatal services. The primary outcome is maternal competence. Secondary measures include paternal competence, parental stress, parental mentalizing, and infant socioemotional development. Analysis will employ survey data and data from the health visitors’ register.

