## Methods

### Study design

The study is designed as a controlled parallel group study with two arms, with the control group of parents receiving the existing publicly available postnatal care services in the 10 municipalities, i.e. Care As Usual (CAU), and the intervention group of parents receiving the Understanding Your Baby (UYB) integrated in to the existing publicly available postnatal care services (i.e. CAU). Both groups come from the same 10 municipalities. The CAU group is included in the project’s first phase and when data collection for this group is finished, all health visitors in the 10 municipalities are trained in delivering the UYB intervention. When the health visitors have finished their training, the UYB group is included in the project’s second phase.

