### Dates defining periods of recruitment and follow-up

The project’s first phase, i.e. recruitment of the CAU group, began May 15th, 2019 and ended February 29th, 2020. This group includes parents and their infants born from April 1st until September 30th, 2019 in the 10 municipalities. In August 2020, the health visitors began training in the UYB-intervention. However, due to COVID-19, the training of the health visitors in three of the 10 municipalities had to be postponed and was finished by March 2021. In seven municipalities, the project’s second phase, i.e. the recruitment of the UYB group, will take place in the period from February 15th until November 30th, 2021. This group includes parents and infants born from January 1st until June 30th, 2021. In the three municipalities where the UYB training was delayed, the participant recruitment will take place in the period from May 15th, 2021 until February 28th, 2022. This group includes parents and infants born from April 1st, 2021 and until September 30th, 2021. Data collection will go on until December 2022.

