As described previously, the data collection for the study started in May 2019, with the data for the CAU group being collected between May 2019 and September 2020 and the data for the UYB group being collected between February 2021 and December 2022. With the first Danish patient testing positive for COVID-19 in February 2020 and the first national lockdown beginning in March the same year, the data collection for the CAU and UYB groups has taken place during a period where COVID-19 lockdowns and restrictions have affected the everyday lives of most adults and children in Denmark. However, since the first lockdown came while the data collection for the CAU group was well under way, it was not possible to implement any new measures in the study that could have been used to measure the influence of COVID-19 on the sample or to measure COVID-19 related differences between the CAU and the UYB group. Hence, an unforeseen but important limitation of the study will be that the COVID-19 lockdowns and constantly changing number of restrictions may have affected the study in a number of ways. Since the restrictions have varied over time, participants in the two groups and participants in each group may have been affected differently by COVID-19, and it cannot be ruled out that the pandemic have affected the primary or secondary outcomes of the study. Furthermore, the heath visitors’ delivery of both CAU and the UYB intervention may also have been negatively affected by the pandemic.

Nonetheless, results from this study will provide new evidence regarding the efficacy of UYB in the 10 municipalities. To the extent that the UYB shows to be a promising approach, health visitors in other municipalities may be trained in UYB in a future up-scaling.

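### The contamination-adjusted ITT is promised without condition as the better estimate, but group is calendar phase, so any phase bias is divided by the delivery rate and the promise is not assured

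*Protocol article*

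**What the plan says.** The protocol article, Statistical methods, analyses all outcomes by CAU or UYB status under intention to treat. It then states that "as a secondary analysis, we will also conduct analyses where the actual intervention participation is taken into account", receipt meaning that the health visitors actually gave UYB to families in the UYB group. The method is named: "Thus, we will perform a contamination adjusted intention to treat analysis [61] which compliments the intention-to-treat approach". The stated advantage is "producing a better estimate of the effect of the UYB intervention", with no condition attached.

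Group status is set by time. The abstract describes data collection as "First in the control group receiving the publicly available postnatal care (CAU), secondly in the intervention group after UYB implementation", and Study design says: "When the health visitors have finished their training, the UYB group is included in the project’s second phase". The section on recruitment dates puts CAU births in April to September 2019 in all ten municipalities. UYB births are January to June 2021 in seven municipalities and April to September 2021 in the other three.

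The Discussion says of COVID-19 that "it cannot be ruled out that the pandemic have affected the primary or secondary outcomes of the study". It adds that the two groups may have been affected differently and that no measure of this could be added. The three covariates are maternal education, depressive symptoms and age.

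**The concern.** A contamination-adjusted ITT is ordinarily an instrumental-variable (Wald) estimate: the group difference in outcome divided by the group difference in receipt. It recovers the effect of receipt if two conditions hold. Group must be unrelated to other determinants of the outcome, and it must act on the outcome only through receipt.

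Randomisation would secure the first condition; calendar phase does not. Period, pandemic restrictions and, in seven municipalities, birth season all differ between the groups.

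The second condition is doubtful too. The UYB videos are open to anyone on the project website and further content is posted on social media, so phase can reach families outside what counts as receipt from the health visitor.

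At stake is how the secondary result will be read. If the groups differ by phase, the adjusted figure attributes that difference to UYB, magnifies it when delivery is incomplete, and arrives described as an improvement on the ITT.

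**Working it through.** **Inputs from the article.** Allocation by phase and the birth windows (Study design; recruitment dates); the three covariates (Statistical methods); 690 analysed participants (Sample size), taken as 690/2 = 345 per group for the simulation. The article gives no numerical result or delivery rate for this analysis, so there is no figure of its own to reproduce.

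**Assumptions.** The estimator has Wald form, which is the usual meaning of the named method; the article does not write it out. Delivery p in the UYB group is 0.5 to 0.9. Phase bias b is 0.05 or 0.10 SD. CAU receipt is set to 0 for simplicity.

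**Step 1: timing.** Adding 11 months to the birth windows puts the primary endpoint at about March to August 2020 for CAU, December 2021 to May 2022 for UYB in seven municipalities, and March to August 2022 in three. Both groups are assessed during the pandemic, but in different periods.

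**Step 2: bias.** Let e be the effect of receipt.
- ITT = e·p + b
- Adjusted estimate = ITT/p = e + b/p

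The part due to UYB is restored to e, and the bias is multiplied by 1/p. With e = 0 the adjusted estimate is:

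| p | 1/p | b = 0.05 | b = 0.10 |
|---|---|---|---|
| 0.9 | 1.11 | 0.056 | 0.111 |
| 0.8 | 1.25 | 0.0625 | 0.125 |
| 0.7 | 1.43 | 0.071 | 0.143 |
| 0.6 | 1.67 | 0.083 | 0.167 |
| 0.5 | 2.00 | 0.100 | 0.200 |

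The corresponding ITT is simply b, 0.05 or 0.10.

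**Step 3: the test.** The standard error is divided by p as well, so the ratio of estimate to standard error hardly moves. A simulation (345 per group, 20,000 runs, no clustering or covariates, e = 0, b = 0.10, p = 0.7) gave a mean ITT of 0.100 and a mean adjusted estimate of 0.143. Rejection at the two-sided 5% level was 25.8% for the ITT and 25.7% for the adjusted analysis. The adjusted 95% interval covered the true value in 74% of runs. With b = 0, rejection was 4.8% for both and coverage 95%.

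**Step 4: which estimate lies nearer e.** The ITT error is b − e(1 − p); the adjusted error is b/p. Take e = 0.2 and p = 0.7.
- b = −0.05: ITT 0.09, adjusted 0.129. The adjusted figure is nearer 0.2.
- b = +0.05: ITT 0.19, adjusted 0.271. The ITT is nearer.

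With e = 0.2 and p = 0.6, the adjusted figure is nearer when b lies between −0.08/(1/0.6 − 1) = −0.12 and 0.08/(1/0.6 + 1) = +0.03.

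**The case against.** The strongest reply is that this is not a defect of the adjusted analysis. The bias comes from the before–after design, the primary ITT carries it unscaled, the Discussion discloses it, and the analysis is secondary and meant to complement the ITT. Accounting for non-receipt is its declared purpose, and it does that. All of this is true, and it limits the point to the claim made for the analysis. It does not rescue that claim: the Discussion never connects the limitation to this analysis, and Statistical methods attaches no condition.

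Several stronger readings are tempting but unsupported.

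- *The adjusted estimate is the worse one.* Step 4 shows that either can be nearer the effect of receipt, depending on the direction and size of b, which the article does not give.
- *The conditions are shown to fail.* The Discussion concedes a possible effect of unknown size and direction, no more. The season difference does not arise in the three delayed municipalities, whose birth months match CAU.
- *The inflated bias can exceed the planned effect*, for instance 0.10/0.4 = 0.25 against d = 0.2. That mixes scales, since d = 0.2 is for group status. At p = 0.6 an ITT effect of 0.2 corresponds to 0.2/0.6 = 0.333, and bias relative to signal is one half on either scale (0.10/0.20 and 0.167/0.333).
- *CAU receipt is zero, so there is no contamination to adjust.* Training began in August 2020, while the Discussion has CAU data collection running to September 2020. Some overlap, probably small, is possible.
- *A group-by-scheduled-ADBB model should take over.* Birth windows differ between municipalities, so the phase contrast is not common to all, and the dose varies over only ten of them.

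It also stands that the estimator is not written out and that a fuller plan may specify it.

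**Conclusion.** The point holds as a misstatement of what the analysis can deliver. Dividing by receipt corrects dilution from incomplete delivery. It neither removes nor tests a difference between phases, and it carries any such difference forward as b/p. For assumed delivery of 50% to 90%, the multiplier is 2.0 to 1.11; at 100% delivery the two estimates coincide.

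The adjusted estimate is therefore not assured to be better, and the article gives no basis for saying that it is. The adjustment itself adds no false positives: the 26% rejection rate in the simulation comes from the assumed phase bias and is the same for the primary ITT.

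This rests on the usual instrumental-variable reading of the named method and on assumed values of b and p. The primary analysis plan is untouched. What changes is what the trial may conclude from this secondary analysis.

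**What to change.** - Delete the claim that the analysis yields a better estimate.
- State that it assumes no difference between the phases other than UYB, and that group acts on the outcome only through receipt as measured.
- Label it exploratory and base no efficacy conclusion on it.
- Report the delivery rate in each group. Table 3 collects implementation intensity for the UYB group only, so any CAU receipt would have to come from visit dates set against the registered training attendance.
- Beside the estimate, tabulate (ITT − b)/p over a stated range of b in both directions. If any CAU families received UYB, replace p by the difference in delivery.

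The cost is a few sentences and one small table, with no new data from parents. The downside is a less favourable description of a secondary analysis.
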